### Interim analyses {21b}

An interim analysis is planned after enrollment of 12 participants for each group. Results and implications will be discussed with the project statistician, sponsor-investigator, and medical expert. An alpha power function based on O’Brian-Fleming boundaries will be used for alpha allocation at interim and final analysis. Details of the statistical significance cut-off are provided in the “Statistical methods for primary and secondary outcomes {20a}” section. In addition, a non-binding futility boundary of zero effect will be selected.

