Role of sponsor {5c}	[name] is the Sponsor-Investigator and one of the operating surgeons in the study. Together with his surgical team, he will recruit patients, inform them about the study and obtain informed consent. He will be responsible for performing the surgeries and collecting the data. After surgery, he will provide the data to the other authors of the study for further processing, analysis, and interpretation, and will write the report. He has final authority over all activities.

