### Outcomes {12}

#### Primary

The primary outcome of our prospective study is operating time. It is the most important and decisive parameter in our comparison between 3D HD and 2D 4K and potentially influences our secondary outcomes. In summary, operative time has a significant impact on a patient’s postoperative outcome and is therefore of considerable clinical relevance. Operative time is measured and documented during the performance of laparoscopic gastric bypass. It is defined as the time from the beginning of the operation by the incision of the skin to the end of the operation by the end of the skin suture. The operative time is the difference between these two times and is documented in minutes.

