### Implementation {16c}

Patients are randomized 1 day before surgery using a computer-generated allocation list (generated using R version 4.1.3). The randomization list is linked to the study’s data management program (REDCap) by the project statistician. The operating surgeon recruits the patients and collects the data needed to conduct the study. The day before surgery, the surgeon enters the data into the electronic case report form (eCRF) in REDCap, which is designed for this study. Once the patient is enrolled in the study and the required data is entered into the system, the patient is automatically assigned to an intervention group using the linked randomization list. This ensures that surgeons have no influence on patient allocation. However, they are unblinded and are informed on the preoperative day which laparoscopic system will be used for the next surgery in the study. This is unavoidable, which is why our study is single-blind. Only the patients are blinded.

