## Oversight and monitoring

### Composition of the coordinating center and trial steering committee {5d}

This is a monocentric study designed, conducted, and coordinated at the University Hospital of Basel. The day-to-day management of the study is carried out by the following:Sponsor-investigator: takes over the supervision of the study and the medical responsibility for the patients, in addition he is one of the three defined operators of the studyMedical expert: advises, conducted the corresponding preclinical study comparing 2D 4K vs. 3D HD on a pelvitrainer model [8]Study coordinator: enrollment, coordination of study visits, annual safety reportsStatistician: organizes data collection, ensures quality, and analyzes dataOther investigators/operators: recruit, obtain consent, operate, and ensure follow-up according to protocol

The study team meets as needed, but not regularly. There is no study steering committee or stakeholder/public engagement group.

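### Interim arm-level operating times are to be discussed with the sponsor-investigator, one of three unblinded operators who will perform some of the remaining cases

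*Protocol article*

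**What the plan says.** The interim section ({21b}) fixes the timing, "An interim analysis is planned after enrollment of 12 participants for each group", and names who takes part: "Results and implications will be discussed with the project statistician, sponsor-investigator, and medical expert". Under {20a} the primary comparison is an independent t-test of operating time between the groups, so the interim results are comparative.

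Under {5c}, the person named "is the Sponsor-Investigator and one of the operating surgeons in the study". The same entry adds "He will be responsible for performing the surgeries and collecting the data" and "He has final authority over all activities". Section {5d} confirms the operating role: "in addition he is one of the three defined operators".

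On blinding of surgeons, {16c} says: "However, they are unblinded and are informed on the preoperative day which laparoscopic system will be used". Only patients are blinded ({17a}). The primary outcome runs from "the incision of the skin to the end of the operation by the end of the skin suture", in minutes ({12}).

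There is no data monitoring committee, on grounds of low risk and safety handling ({21a}), and no steering committee ({5d}). The futility bound is zero effect and non-binding ({20a}, {21b}).

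**The concern.** An operator who knows which system is in use will have been shown which arm is ahead, by how many minutes and with what p-value, while half of the 48 patients are still to be operated on. The endpoint is elapsed time from first incision to last suture, so the operator's pace enters it directly. The trial also has a stated directional hypothesis, that 3D HD is faster ({7}).

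Group sequential boundaries account for testing the same accumulating data twice. They assume that the treatment contrast in the later data is not altered by the look. If an operator who has seen the result becomes faster or slower in one arm relative to the other, the final test no longer has its nominal error rate and the estimate is biased. No later analysis can fully separate that change from a true effect.

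**Working it through.** **Step 1. Reproduce the design.** Inputs from {14} and {20a}: one-sided alpha 0.025, two looks, O'Brien-Fleming-type spending, difference 15 min, SD 15 min, power 90%, futility bound 0.

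- Alpha spent at half information: 2[1 − Φ(z₀.₉₈₇₅/√0.5)] = 0.001525, against 0.0015 stated.
- Final boundary from the bivariate normal with correlation √0.5: z = 1.969, one-sided p = 0.0245, as stated.
- Fixed-sample t-test N = 44.04; inflation factor 1.0116; 44.04 × 1.0116 = 44.55 in total and 22.28 at interim, against 44.6 and 22.3 stated.

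The design arithmetic is sound. The point concerns conduct only.

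**Step 2. Who sees what, and when.** The interim uses 12 + 12 = 24 patients, leaving 48 − 24 = 24 cases, 12 per arm. {21b} names the sponsor-investigator in the discussion; {5c} and {5d} make that person an operator; {16c} gives operators the arm in advance; {12} makes pace part of the outcome.

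**Step 3. Illustrate what is at stake.** These inputs are assumptions, not figures from the protocol: no true difference; a one-third share of post-interim cases (one of three operators, actual share not stated); a shift of h = 5 or 10 min in favour of 3D in that operator's post-interim cases. SD 15 and 24 per arm come from the plan.

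- Average post-interim shift in the contrast: h/3 = 1.67 or 3.33 min.
- Bias in the final estimate, since half of each arm is post-interim: (12/24) × h/3 = h/6 = 0.83 or 1.67 min.
- Standard error of the final difference: 15 × √(2/24) = 4.33 min.
- Approximate rejection rate: 1 − Φ(1.969 − bias/4.33). For h = 5: 1 − Φ(1.78) ≈ 3.8%. For h = 10: 1 − Φ(1.58) ≈ 5.7%.

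Simulating the t-test at the planned critical value gives about 3.7% and 5.4%. The normal approximation runs slightly high because it ignores the t distribution and the extra spread when only some cases shift. A separate simulation using both boundaries and a uniform 1.67 min shift gives about 3.8%, and about the same if the shift occurs only after an interim trend favouring 3D. With no shift, the simulated rate is about 2.5%.

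**Step 4. Effect of the remedy on the design.** Restricting who sees the comparison changes no input in Step 1, so N (44.6, 48 recruited) and the critical p-values (0.0015, 0.0245) stand.

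**The case against.** The strongest reply is that the interim look is not the main source of exposure. The sponsor-investigator operates unblinded and collects the data ({5c}, {16c}), and so already holds arm and operating time for their own cases and could tabulate the rest. This stands in part: only the increment from seeing a formal comparison belongs to the look, and the documents give no means of estimating it. It also means that withholding the interim summary alone is weak unless pooled arm-level exports are withheld as well.

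A reader might infer that type I error reaches 8% to 18%. That requires a 5 to 10 min arm-differential shift in every post-interim case by all three surgeons. {21b} names only one operator, and nothing says that the results will reach the other two. The protocol's limitations section also notes many influences on operating time besides the imaging system, so the outcome is influenced by the surgeon rather than controlled by the surgeon.

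A reader might also infer that the disclosure opens the way to case selection. Support for this is weak. Patients have already chosen surgery ({15}), and assignment is automatic once data are entered ({16c}). Replacing patients excluded before surgery ({11b}, {16a}) is a separate matter that exists without an interim look.

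There is partial mitigation. The operator of each case and the surgeons' leaning towards either system are recorded ({12}), and an independent monitor verifies key data ({23}). These allow checks by surgeon but do not prevent a change of pace.

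Finally, a condensed article may leave interim access rules to the full protocol or SAP. The point therefore does not rest on a missing safeguard. It rests on the article's explicit inclusion of an operator in the discussion of results.

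**Conclusion.** The point holds as a stated design choice that should be changed. Comparative interim results on the primary outcome go to a person who will perform some of the 24 remaining operations with knowledge of the arm. The low-risk argument for having no monitoring committee concerns safety and does not address who may see comparative efficacy data.

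Under the assumptions in the working, one-sided type I error rises from 2.5% to about 3.7-5.4% and the estimate is biased by about 0.8-1.7 min, against a design difference of 15 min. The shift size, its direction and the case share are all assumed. The effect would be larger only if the results also reached the other operators. A change of pace common to both arms would not bias the contrast. The documents do not show that any such change will occur, nor that the boundaries or the sample size are wrong.

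**What to change.** Rewrite the interim section ({21b}) along these lines:

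- The project statistician, who already receives the data export for the interim under {19}, runs the look and applies the stated efficacy and futility boundaries.
- Arm-level results go to the medical expert only if that person does not operate, recruit or collect outcome data in the trial. The article does not say whether this is so. It does say that the expert conducted the preclinical study ({5d}) on which the hypothesis rests ({7}), so the expert's role should be stated. Otherwise the results stay with the statistician.
- The sponsor-investigator and the other operators are told only to stop or continue. They receive no arm means, p-values, effect estimates or pooled arm-level data exports until the last operation is done.

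If the look has already taken place (recruitment began in August 2023), document who saw the results and report the treatment difference separately before and after the interim.

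The cost is one paragraph, with no change to sample size or boundaries and no new staff. The sponsor-investigator gives up personal discretion over the non-binding futility stop. The remedy reduces the exposure but does not remove it, because operators will still know their own cases.

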### Methods for additional analyses (e.g., subgroup analyses) {20b}

There are no subgroup analyses planned.

### Methods in analysis to handle protocol non-adherence and any statistical methods to handle missing data {20c}

To ensure data quality, the monitoring plan checks the data for missing data, extreme outliers, and erroneous entries prior to statistical analysis. Missing data will be closely monitored. However, missing data due to noncompliance or dropout should remain within the expected minimum. Dropouts related to the primary outcome will be replaced to achieve the required number of participants and thus significant results. There is no need to replace dropouts for the secondary outcomes, and there are no plans to use multiple imputation.

### Plans to give access to the full protocol, participant-level data, and statistical code {31c}

The datasets used and/or analyzed in the current study can be made available by the corresponding author upon reasonable request and in accordance with the research collaboration and data transfer guidelines of the University Hospital Basel.

## Oversight and monitoring

### Composition of the coordinating center and trial steering committee {5d}

This is a monocentric study designed, conducted, and coordinated at the University Hospital of Basel. The day-to-day management of the study is carried out by the following:Sponsor-investigator: takes over the supervision of the study and the medical responsibility for the patients, in addition he is one of the three defined operators of the studyMedical expert: advises, conducted the corresponding preclinical study comparing 2D 4K vs. 3D HD on a pelvitrainer model [8]Study coordinator: enrollment, coordination of study visits, annual safety reportsStatistician: organizes data collection, ensures quality, and analyzes dataOther investigators/operators: recruit, obtain consent, operate, and ensure follow-up according to protocol

The study team meets as needed, but not regularly. There is no study steering committee or stakeholder/public engagement group.

### Composition of the data monitoring committee, its role and reporting structure {21a}

No specific DSMCs are required for this category A1 study. All interventions performed and the product tested are associated with extremely low risk factors, and therefore, any potential safety issues can and will be reported and handled in plenary by the sponsor-investigator and responsible personnel.

### Adverse event reporting and harms {22}

All adverse events (AEs), device defects (DDs), and serious adverse device effects (SADEs) reported by subjects or observed by investigators will be collected, fully investigated, and documented in the source document and appropriate case report form (eCRF; symptoms/diagnosis, event onset and cessation, event treatment and resolution, assessment of relationship to MD and/or investigational procedure) throughout the trial period. An annual safety report (ASR) will be submitted by the sponsor-investigator to the competent ethics committee (CEC) on an annual basis.

### Frequency and plans for auditing trial conduct {23}

Monitoring will be performed by a monitor (CRA) independent of the study team in accordance with ISO 14155. Based on the risk-based monitoring (RBM) score calculator of the Swiss Clinical Trial Organization (SCTO) monitoring platform, the estimated risk for this study is considered low. Based on this, monitoring will be limited to random visits (on-site and remote), including verification of the presence and completeness of the study file and CDM by the monitor, and will be the responsibility of the sponsor-investigator. CDM (with full SDV of key data) will be performed each time new subjects are enrolled or at least every 3 months. Data will be validated by persons authorized by the sponsor-investigator and under the supervision of the monitor prior to interim analysis (after *n* = 12 per group) and prior to final analysis. The monitoring plan can be consulted for further information. Possible inspections by health authorities may take place, where the source data/documents will be accessible to the inspectors and questions will be answered.

### Plans for communicating important protocol amendments to relevant parties (e.g., trial participants, ethical committees) {25}

The trial will be conducted in accordance with the protocol and the tenets of the Declaration of Helsinki in its current version, the European Medical Device Directive 2017/745 (MDD), ISO 14155 and ISO 14971 standards, ICH Good Clinical Practice (GCP) guidelines, as applicable, the Swiss Human Research Act (HRA) and its ordinances, and the requirements of the Swiss regulatory authority. No changes will be made to the protocol without prior approval of the sponsor-investigator and the Ethics Committee of Northwestern and Central Switzerland (EKNZ), except when necessary to eliminate obvious immediate hazards to subjects. All substantial amendments will be submitted to the EKNZ. Non-substantial changes are recorded and filed. They will be submitted to the EKNZ together with the annual safety report (ASR). If the changes concern or affect the participants in any way, they will be informed of the changes. If necessary, the registration in the SNCTP and in the primary WHO registry (ClinicalTrials.gov ) will be adjusted.

### Dissemination plans {31a}

International peer-reviewed journals will be used to fully disclose the results of this research. Both positive and negative results will be reported. Upon request, participants will receive a summary of the overall results of the study.

## Discussion

This randomized controlled prospective study is designed to compare 2D 4K vs. 3D HD laparoscopic imaging during gastric bypass surgery. The aim is to test the hypothesis that 3D HD laparoscopy can lead to significantly shorter operative times compared to the use of newer, high-quality 2D 4K laparoscopic systems in bariatric surgery. The results will be used to gather evidence on the imaging of modern laparoscopy. This evidence can then be used to focus on the advantages of modern imaging systems, to use them in a more targeted way, and to achieve better outcomes in laparoscopic surgery.

## Limitations

There are some limitations to be considered. First of all, it should be mentioned that, in daily practice, the laparoscopic imaging system is chosen according to the surgeon’s preference and the availability of medical equipment. As a result, the surgeon’s skills may adapt to the more common laparoscopic conditions. This represents a potential bias for direct comparison. To minimize this, we selected a team of three senior surgeons with extensive experience with both laparoscopic imaging systems. It is also important to note that there are many possible influences on operative time and secondary outcomes that are independent of the chosen laparoscopic imaging system. Due to the strict indication criteria for gastric bypass, the patients in the study should have similar conditions and therefore provide similar operative circumstances as much as possible. Comparability is further supported by the highly standardized nature of the gastric bypass procedure. In addition, it is important to mention that there is a general limitation of 4K technology due to the requirement of large size monitors (e.g., 55″) to benefit from the ultra-high resolution. When this is not the case, as in our randomized controlled trial or in the reality of many operating rooms, the surgeon should be close to the monitors to take full advantage of the 4K resolution. Otherwise, the 4K technology cannot be assumed to have an advantage.

## Strengths

This clinical trial will compare the two newest laparoscopic imaging systems available. As there is currently little relevant clinical literature on such a comparison in bariatric surgery, there are no significant disadvantages or even risks for patients participating in this study, regardless of which group they belong to. Both groups receive gastric bypass according to current standards. In contrast, further evidence on the two laparoscopic systems should provide some clinical advantages. As laparoscopic surgery continues to grow in popularity, clear evidence for the targeted use of laparoscopic imaging systems may further enhance its benefits. If 3D HD laparoscopy effectively leads to shorter operating times compared to 2D 4K systems, its targeted use in multiplane procedures such as gastric bypass may lead to better surgical outcomes for the patient. This in turn may have cost savings implications that may be of greater importance in the future as laparoscopic surgery gains momentum.

## Trial status

The current protocol is Version 2.0 of 08/04/2023. Recruitment started in August 2023. Patient recruitment is estimated to be completed June 2025.

## Abbreviations

AE: Adverse event
ASR: Annual safety report
CDM: Central data monitoring
CEC: Competent ethics committee
CRA: Clinical research associate
eCRF: Electronic case report form
2D: Two-dimensionality
3D: Three-dimensionality
DD: Device deficiency
DSMC: Data safety monitoring committee
EAES: Association for Endoscopic Surgery
GCP: Good Clinical Practice
H0: Null hypothesis
H1: Alternative hypothesis
HRA: Federal Act on Research involving Human Beings
ISO: International Organization for Standardization
MD: Medical device
MDR: Medical Device Regulation (EU) 2017/745 of 5 April 2017
LRYGB: Laparoscopic Roux-en-Y gastric bypass
OT: Operating time
SADE: Serious adverse device effect
SDV: Source data verification
SMOB: Swiss Morbid Obesity Group
SNCTP: Swiss National Clinical Trials Portal
